### Adherence to treatment

At the end of each telephone session, LPs will take note of the pages read and the exercises completed by the participant during the previous week. They will also take note of the content covered during the session. Furthermore, LPs will evaluate each of the following aspects on a scale ranging from 0 (very weak) to 8 (very good): (1) degree of participant implication with regards to self-treatment, and (2) overall assessment of the quality of the collaboration perceived during the interview.

The degree to which LPs have adhered to the specified tasks assigned to them will also be assessed. All sessions for each participant will be recorded and divided in three parts. An equivalent number of sessions in each part will be randomly selected to obtain 25% of sessions. The integrity of these sessions will be verified by an independent evaluator using a first list of acceptable procedures (e.g., proving motivational support) and a second list of procedures that should not be used (e.g., recommending thought stopping and distraction). The first list will only include procedures presented during training. The evaluator will record the time spent on each procedure. The time spent on procedures in the first list compared to the total time of the session will be calculated.

### Data management and analysis

The principal investigators (PL, PG, and SG) will have access to all trial data. To protect the identity of participants and confidentiality of information, participants will be identified by a code number. Data obtained by paper questionnaires will be kept in a secure file. Data in electronic format will be kept on a secure server accessible to the research team only. Research assistants will double-entry data in paper format in order to detect and correct data entry errors. Data obtained from online questionnaires will be added to the data files.

SPSS for Windows will be used for statistical analyses. Missing data will be handled using multiple imputation. Descriptive analyses of study variables will be carried out. Analyses will follow intention-to-treat principles (i.e., data from all participants included in the study will be analyzed according to the randomization scheme). The pre- and post-treatment data will be used to compare the experimental and control groups. Repeated measures analysis of variance (ANOVA) will be performed on most outcome measures. Simple effects for group and time and group by time interactions will be analysed. Between group comparisons will include remission rate based on GAD diagnosis using the chi square test and clinically significant change which will be examined according to procedures described by Jacobson et al. [65, 66]. Change on the Sheehan Disability Scale will be analysed according to Sheehan and Sheehan’s [67] criteria. In order to determine whether the effects of the treatment are sustained over time, the post-treatment, 6 and 12-month data of the experimental group will be used. Repeated measures ANOVA will be carried out on the different variables and followed by contrast analyses. All model assumptions will be checked. Participants’ and LPs’ perception of treatment will be analyzed by calculating the frequency of each answer choice for the various statements and by summarizing comments.

The relationship between variables and improvement during treatment will be examined by combining the two groups’ pre- and post-treatment data. A change ratio will be calculated for each measure of GAD symptoms in order to obtain a score representing treatment response. Univariate analyses will be performed first using Pearson correlations for continuous variables and ANOVAs for categorical variables. Subsequently, variables that are significantly related to a change on each GAD symptom measure will be retained for a stepwise multiple regression analysis on this measure to identify the best predictors of change.

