**Methods:**

We will conduct a multisite randomized controlled trial comparing an experimental group receiving GSH-CBT guided by LPs (*n* = 45) to a wait-list control group (*n* = 45). Treatment will last 15 weeks and will be based on a participant’s manual. Weekly telephone sessions with LPs (30 min maximum) will be limited to providing support. Data will be obtained through clinician evaluations and self-assessment questionnaires. Primary outcomes will be the tendency to worry and severity of GAD symptoms. Secondary outcomes will be anxiety symptoms, sleep difficulties, functional deficit, diagnosis of GAD, and cognitive difficulties. For the experimental group, measurements will take place at pre- and post-treatment and at 6 and 12 months post-treatment. For the control group, three evaluations are planned: two pre-treatment evaluations (before and after the waiting period) and after receiving treatment (post-treatment). The efficacy of GSH-CBT will be established by comparing the change in the two groups on the primary outcomes.

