## Methods

### Trial design

This is a multisite randomized controlled trial comparing an experimental group receiving GSH-CBT guided by LPs to a wait-list control group. The control group will receive GSH-CBT after the waiting period. Because this is a wait-list condition, we will provide no active treatment to participants in this group during the waiting period. This will also maximize their response to GSH-CBT and allow us to include their data in analyses to identify characteristics associated with improvement during treatment. Data will be collected at pre-treatment, post-treatment and 6 and 12 months post-treatment. A multisite study will allow the recruitment of the required sample and increase the generalizability of the study. Université Laval will act as the study sponsor. The study will take place at three sites (Université Laval, Université de Sherbrooke, and Centre de recherche de l’Institut universitaire de gériatrie de Montréal) and patients at each site will be recruited into both intervention groups. A schematic representation of the randomized controlled trial is shown in Fig. 1.

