A block randomization procedure stratified on diagnosis will be used. The randomization sequence will be determined prior to recruitment by the project coordinator. Block size will be fixed at 4, all possible balanced combinations of assignments within a block will be identified, and blocks will be randomly chosen to determine participants’ assignment to groups. Randomly assigned conditions will be sealed in envelopes labelled with participant codes and opened by the project coordinator following completion of the pre-treatment assessment. Group assignment will be done separately for participants with threshold and subthreshold GAD. Participants assigned to the experimental group will begin treatment immediately after the pre-treatment assessment. Participants assigned to the control group will have a 15-week wait period, during which they will receive a 15-min telephone call from the local professional research assistant on four occasions separated by four-week intervals. The purpose of these calls is to encourage the participant to persevere until the start of treatment and to identify potential negative effects that could be associated with the waiting period. For the experimental group participants, assessments will take place at pre- and post-treatment and at 6 and 12 months post-treatment. For control group participants, three assessments are planned: two at pre-treatment (before and after the waiting period) and one after receiving treatment (post-treatment). All participants will receive financial compensation ($20 CAD) for each of the post-treatment and follow-up assessments to support participation in post-treatment assessments.

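### The efficacy rule uses visit labels that point to the wrong control assessment; as worded, the payment rule also omits the control arm's deciding visit

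*Protocol article*

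**What the plan says.** The section on data management and analysis sets the data for the between-group test: "The pre- and post-treatment data will be used to compare the experimental and control groups".

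The Procedure section defines the visits. For the experimental arm: "For the experimental group participants, assessments will take place at pre- and post-treatment and at 6 and 12 months post-treatment". For the control arm three assessments are planned: "two at pre-treatment (before and after the waiting period) and one after receiving treatment (post-treatment"). The Abstract uses the same labels: "two pre-treatment evaluations (before and after the waiting period) and after receiving treatment (post-treatment"). On timing, "Participants assigned to the control group will have a 15-week wait period", and under Trial design, "The control group will receive GSH-CBT after the waiting period".

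Two further rules rest on the same labels:

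- **Predictor analysis** (end of the analysis section): "The relationship between variables and improvement during treatment will be examined by combining the two" groups' pre- and post-treatment scores.
- **Payment** (Procedure): all participants receive "financial compensation ($20 CAD) for each of the post-treatment and follow-up assessments".

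**The concern.** The randomised comparison is between people who have had GSH-CBT and people who have only waited. In the control arm, the visit that carries it is the end-of-wait assessment. The protocol labels that visit pre-treatment, and the efficacy rule does not name it. The control visit labelled post-treatment comes after that arm has been treated as well. The rule's wording therefore conflicts with the contrast the trial was designed to test.

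The same sentence governs the primary outcomes and, by its position, the other between-group comparisons in that paragraph, including remission and clinically significant change. A reader must override the protocol's own definitions to run the intended analysis.

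Two consequences follow from the same labels. In the predictor analysis, controls have two pre-treatment scores and the text does not say which one starts the change ratio. In the payment rule, the visit that decides the trial attracts an incentive in one arm and, on the wording, none in the other.

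**Working it through.** **1. Visits on a common clock, from the Procedure and Treatment sections (15-week wait, 15-week treatment)**

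| Approximate time from randomisation | Experimental arm | Label used | Control arm | Label used |
|---|---|---|---|---|
| Before allocation | untreated | pre-treatment | untreated | pre-treatment (before wait) |
| 15 weeks | treated | post-treatment | untreated | pre-treatment (after wait) |
| 15 + 15 = 30 weeks | – | – | treated | post-treatment |

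The intended contrast is the 15-week row, adjusted for or compared with the first row. Matching on the label post-treatment instead pairs the experimental arm at 15 weeks with the control arm at about 30 weeks, when both have been treated.

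**2. Which contrast is intended**

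- The hypothesis (end of Background) is greater improvement than in the wait-list group.
- The effect size (Participants) is a difference between the treatment group and the wait-list group.
- The Abstract bases efficacy on comparing change in the two groups.
- Trial design gives the controls' treated data a separate use: finding characteristics associated with improvement.

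All four fit the 15-week row.

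**3. The same phrase in the predictor analysis**

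That analysis concerns improvement during treatment, so the control post-treatment score must be the one after GSH-CBT. In adjacent paragraphs the same phrase therefore has to mean two different control visits.

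The two possible control baselines give different intervals. End of wait to post-treatment covers about 15 weeks, all treated. Before wait to post-treatment covers about 30 weeks, of which 15 are untreated. Only the first matches the experimental arm's 15 weeks.

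**4. The plan's sample size, and power for the intended contrast**

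Inputs from the Participants section: d = 0.65, alpha 0.05, power 0.80, 45 per group, 30% drop-out, 130 admitted. Sidedness is not stated, so two-sided is assumed.

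- n per arm = 2(1.960 + 0.842)² / 0.65² = 37.2, so 38. The t-test solution is 38.1, so 39. The total is 76 to 78, against 90 stated. The stated figure is not reproduced, but it errs on the large side. This is a separate matter and does not bear on the present point.
- 90 / (1 − 0.30) = 128.6, so 129, against 130 stated. This agrees.
- Power at 45 per arm: 0.65 × √(45/2) = 3.08, and Φ(3.08 − 1.96) = 0.87. The t-test gives 0.86.

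Correcting the label changes neither the sample size nor this power.

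**5. Payment at the visit that decides the trial**

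- Experimental arm, 15 weeks: labelled post-treatment, so $20.
- Control arm, 15 weeks: labelled pre-treatment, so neither post-treatment nor follow-up, and $0 as worded.
- Control arm, about 30 weeks: labelled post-treatment, so $20, for data outside the randomised contrast.

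Cost of paying controls at 15 weeks: 130 / 2 = 65 and 65 × $20 = $1,300 CAD if every admitted control attends.

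**The case against.** The strongest reply is that no informed reader would compare treated with treated. The hypothesis, the effect size and the Abstract all point to treatment versus wait-list, and Trial design sends the controls' treated data to another analysis. This stands, and it fixes how the point must be put: the wording is wrong, the design is not.

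The baseline is also less open than it looks. The Procedure section has the allocation envelopes opened once the pre-treatment assessment is complete, so the pre-randomisation score is the natural baseline for the efficacy test. In the predictor analysis, the stated aim of studying improvement during treatment points to the end-of-wait score. Both can be inferred, but neither is written in the analysis rule.

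Figure 1 and Table 2 are not shown. The legend of Table 2 defines a week index covering treatment or waiting, which suggests a common time axis. The schedule may therefore be clearer than the text. That would not correct the sentence in the analysis section, which is a stated rule rather than a detail left to a fuller document.

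On payment, it can be said that the text never states outright that the end-of-wait visit is unpaid, that controls receive four encouraging calls and are waiting for treatment, and that missing data will be multiply imputed. These points limit the worry. They do not remove the asymmetry in the rule as worded, whose stated purpose is to support attendance at post-treatment assessments.

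**Conclusion.** The point holds as a labelling error in the primary analysis rule. Read with the protocol's own visit labels, the rule names a control visit that conflicts with the intended contrast, and the neighbouring predictor analysis needs the same phrase to mean something else.

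A reader might infer that the trial will compare two treated groups and so have power close to alpha. The documents do not support that. It would be the rejection probability of an analysis that the hypothesis, the effect size and the Abstract show is not planned, and it further assumes equal effects in both arms. If the intended contrast is analysed, no loss of power is expected.

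The payment asymmetry is a separate, smaller matter. As worded it is $20 against $0 at the primary-endpoint visit. Its effect on missingness cannot be sized: the 30% drop-out is an overall figure and says nothing about a difference between arms. A reader might also take it as settled that controls go unpaid at that visit. That rests on the wording alone, with Table 2 not shown.

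**What to change.** 1. **Efficacy rule.** State that the between-group comparison uses the pre-randomisation assessment in both arms and the 15-week assessment, meaning post-treatment in the experimental arm and end of waiting period in the control arm. Apply this to all between-group comparisons in that paragraph.
2. **Predictor analysis.** State that the controls' pre-treatment score is the end-of-wait score, so that untreated change over the wait is not counted as treatment response.
3. **Payment.** Give the same $20 at the control end-of-wait assessment, or confirm in the text that it is already given.

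The first two changes cost a sentence each. The third costs at most about $1,300 CAD. Sample size, visits and treatment are unchanged.

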### Participants

A power analysis was performed based on the Penn State Worry Questionnaire (PSWQ [39]), which is traditionally used as the primary measure of change in studies of CBT for GAD with older adults. Assuming an effect size of .65 (difference in standard deviations between the scores of the treatment group and the wait-list group with telephone support, based on the work of other researchers [41] and a conservative estimate), an alpha threshold of .05 and power of .80, 90 participants are required (45 in each group). In anticipation of an estimated 30% drop-out rate based on previous work [41], a total of 130 people will be admitted to the study (accepted for treatment) in order to obtain the required number of 90. The maximum proportion of participants with a diagnosis of subthreshold GAD will be set at 40% of the sample. This percentage is similar to that in the study by Jones et al. [25] and reflects the priority given to GAD.

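### The deciding group-by-time ANOVA is a valid test of change, but it does not use baseline as a covariate or name the diagnosis stratum; ANCOVA would be more precise at no cost, and the sample size was worked out for a different contrast.

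*Protocol article*

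**What the plan says.** In the protocol article, Methods, Data management and analysis, the two arms are compared on their pre- and post-treatment data: "Repeated measures analysis of variance (ANOVA) will be performed on most outcome measures". The effects to be examined follow: "Simple effects for group and time and group by time interactions will be analysed". No covariate is named for this comparison. The Abstract adds that efficacy will be judged by comparing change between the arms on the primary outcomes, which are the PSWQ and the GAD-7.

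Under Procedure, "A block randomization procedure stratified on diagnosis will be used", with threshold and subthreshold GAD assigned separately. Site is not a stratification factor.

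Under Participants, the sample size rests on the PSWQ and an effect of .65, described as a "difference in standard deviations between the scores of the treatment group and the wait-list group with telephone support". With "an alpha threshold of .05 and power of .80, 90 participants are required (45 in each group"), and allowing for 30% drop-out, 130 people are to be admitted. No pre-post correlation is given.

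**The concern.** The article names its model and so makes a choice. That choice leaves precision unused. A change score subtracts the whole baseline value whatever the correlation between baseline and outcome, whereas ANCOVA estimates how much of it to subtract. The weaker the correlation, the more noise the change score carries.

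There is also a mismatch with the sample size. A difference between scores and a difference between changes have different variances unless r takes one particular value, and the article gives nothing from which to convert one into the other. The reader therefore cannot tell whether the test that decides efficacy has the stated power of .80.

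Finally, diagnosis was important enough to stratify on, but it is not among the effects listed for the analysis. At stake is the width of the confidence interval on both primary outcomes and, if r is low, the planned power itself.

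**Working it through.** **Inputs from the article (Participants; Data management and analysis).** d = .65 on the PSWQ, alpha .05, power .80, 45 per arm, two time points in the group comparison.

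**Assumptions.** The test is two-sided (sidedness is not stated). The .65 is in units of the post-treatment SD. The pre-post correlation r is not in the article, so a range is shown. Pre and post SDs are taken as equal first, and this is then relaxed.

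**Step 1: the article's own figure.** A two-sample t-test at d = .65, alpha .05 and power .80 needs 38.1 per arm, so 39, or 78 in total (76 by the normal formula). The stated 90 is larger. At 45 per arm, a comparison of post-treatment scores has power .86. So 45 per arm has some slack for a contrast of scores, and that slack is already included in everything below. The drop-out step checks: 90/0.7 = 128.6, and 130 × 0.7 = 91.

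**Step 2: variances, in units of the post-treatment variance, equal SDs.**
- Post-treatment score alone: 1
- Change score (the group-by-time test): 2(1 − r)
- ANCOVA on baseline: 1 − r²
- Ratio of ANCOVA to change: (1 − r²) / [2(1 − r)] = (1 + r)/2, which is below 1 for any r < 1

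The effective standardised effect is .65 divided by the square root of the variance. For r = .3, the change test has .65/√1.4 = .549 and ANCOVA has .65/√.91 = .681.

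**Step 3: power at 45 per arm (two-sample t).**

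| r | change test | ANCOVA | variance ratio |
|---|---|---|---|
| .3 | .73 | .89 | .65 |
| .4 | .80 (.795) | .91 | .70 |
| .5 | .86 | .94 | .75 |
| .6 | .93 | .97 | .80 |
| .7 | .98 | .99 | .85 |

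**Step 4: where the planned test reaches .80.** At 45 per arm, power .80 needs an effective effect of .597, so the change variance may be at most (.65/.597)² = 1.185. With equal SDs, 2(1 − r) ≤ 1.185 gives r ≥ .41.

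**Step 5: unequal SDs.** Let k be the baseline SD divided by the post-treatment SD. The change variance is 1 + k² − 2rk. ANCOVA stays at 1 − r². The difference is (k − r)², so ANCOVA is still never worse. With k = .8:
- r = .3: 1 + .64 − .48 = 1.16, power .81 against .89
- r = .4: 1 + .64 − .64 = 1.00, power .86 against .91
- Threshold for .80: 1.64 − 1.6r ≤ 1.185, so r ≥ .28

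**Step 6: the stratum.** No gain from a diagnosis term can be computed from the article, because it gives no outcome difference between threshold and subthreshold GAD. A difference that stays constant over time cancels in a change score, and in ANCOVA much of it is absorbed by baseline. The reason to include the term is agreement with the randomisation.

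**The case against.** The strongest reply is that both methods are valid. Randomisation makes the change contrast unbiased, and the Abstract openly makes change the basis for efficacy, so this is a matter of efficiency. That stands. So does the condition on the power shortfall: it needs a low r, and the entry criteria could narrow the baseline spread, which lowers the threshold as Step 5 shows. With equal SDs and r above .5, the planned test is more powerful than the score comparison used for the sample size. At r = .7 the gain from ANCOVA is about .01.

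Four stronger readings are tempting, and the article does not support them.
- A reader might infer that baseline is ignored. It is not: it is the first of the two repeated measures. What is true is that it is not used as a covariate.
- A reader might take the listed group effect to be an average over both times, and so partly a pre-randomisation difference. The article says simple effects, which can mean the group difference at one time, and nowhere does it rest efficacy on a time-averaged effect.
- A reader might count site as a dropped design factor. Randomisation was stratified on diagnosis only, so leaving site out contradicts nothing.
- A reader might expect a sizeable further gain from the stratum term. Step 6 shows why none can be claimed.

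It may also be said that a condensed article leaves covariates to a fuller plan. That answers silence. Here the model and its effects are stated, and the recommendation is to change them.

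**Conclusion.** The point holds as an improvement to a stated model that costs nothing. The test that decides efficacy is a t-test on change. Under randomisation, ANCOVA on the same data is at least as precise at every r. With equal SDs it removes (1 − r)/2 of the variance, which is 35% at r = .3 and 20% at r = .6.

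The stated power belongs to a contrast of scores, and the article gives no correlation that would carry it over to a contrast of change. Whether the planned test delivers .80 at 45 per arm is therefore unknown. It does so from r of about .41 with equal SDs, and from just under .3 if the baseline SD is .8 of the post-treatment SD. A reader might infer that the trial is underpowered; the article does not show that, because it gives neither r nor the SDs.

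All power figures assume d = .65 in post-treatment SD units, a two-sided alpha of .05 and 45 analysed per arm.

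**What to change.** For each primary outcome (PSWQ and GAD-7), make the primary analysis an ANCOVA of the post-treatment score, taken at the end of the 15-week wait for controls, on group, the baseline score of that measure and diagnosis stratum. Site may be added but is optional. Fit the model in each imputed data set and pool the group coefficient and its confidence interval by Rubin's rules; a single coefficient suits the multiple imputation already planned.

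Restate the power for this model, with the assumed pre-post correlation and its source, and say whether the test is two-sided. The repeated measures ANOVA can stay as a supporting analysis.

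The cost is wording. Baseline scores and diagnosis are already collected, SPSS fits the model, and no visit, measure or participant is added.
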